### Randomization and blinding

Randomization will be applied within classes, using a random numbers generator (www.randomizer.org), with an equal number of experimental and control groups within one school. Children will be assigned to either video-based transdiagnostic REBT universal prevention or to waitlist control condition. Allocation concealment will be done by an independent researcher, using opaque, sealed envelops that will be opened sequentially. Blinding of participants, researchers and assessors will be maintained.

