### Study conditions

#### The wait-list control group

Participants in the waiting list will not receive an intervention. They will complete assessments at all four time points. They could receive the intervention after the experimental group has completed all the assessments.

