### Video-based transdiagnostic REBT prevention program

The authors, both being certified in REBT from Albert Ellis Institute, New-York, have developed a transdiagnostic REBT protocol for this study by adjusting existent protocols for internalizing problems in adolescents [43, 44]. Namely, our protocol was based on REBT theory [21]. Further, we shortened existent programs in order to investigate the efficacy of a briefer version of the protocol. The prevention program will be delivered in the school context, namely in adolescent’s school classes after regular school hours. The program will consist of six 50 min sessions of video-based REBT (See Table 1 for a content of each session) delivered for three weeks (two times per week) in a group format. Research assistants (Masters students, psychologists trained in CBT) will present each session based on a video cartoon and after this, a standardized PowerPoint presentation will be used to guide the discussion with the adolescents. They will learn various aspects related to internalizing problems, how irrational beliefs influence dysfunctional emotions, how to construct a hierarchy of feared situations and how to expose gradually. Also, they will learn breathing and relaxation exercises. Between sessions, homework will be provided and will be checked at the beginning of each session. The content of each session is presented as follows:

**Table 1 Tab1:** Protocol contents for each session

Session number	Content
1	Psychoeducation regarding internalizing problems
2	How to identify anxiety and depression. Relaxation
3	The ABC model of distress
4	Cognitive restructuring
5	Exposure and behavioral activation. Problem solving
6	Maintenance of therapeutic gains and relapse prevention

Session 1. *Psychoeducation regarding internalizing problems*. In this session, adolescents will be provided with information regarding internalizing problems. Videos regarding different internalizing symptoms will be presented and discussions regarding different types of symptoms will be initiated with the adolescents. Also, they will be informed about the program and about their involvement in this program.

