### Data collection

Adolescents will complete all the assessments at school, in their classrooms, in the presence of a research assistant, blind to group allocation, that will provide assistance if needed. All the instruments will be applied in a paper and pencil format. Adolescents will complete assessments at four time-points: T_1_ (baseline), T_2_ (post-intervention), T_3_ (3 months follow-up) and T_4_ (12 months follow-up). An overview of the instruments that will be used for baseline, post-treatment, 3 months follow-up and 12 months follow-up is provided in Fig. 2.

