Key inclusion and exclusion criteria	Inclusion criteria: Preadolescents and adolescents will have ages between 12 and 17 years old; Are attending middle school or high-school; Adolescents have sufficient understanding of the Romanian language in order to complete assessments at all time points and to participate in the prevention program; Their parents have sufficient understanding of the Romanian language in order to sign the informed consent; Parents will sign the informed consent and adolescents will provide informed assent. Exclusion criteria: Age below 12 or above 17 years; No signed informed consent from parents; Adolescents will score high on suicidal ideation according to (1 item on the Depression subscale from Beck Youth Inventories); Not Romanian-speaking in order to understand the content of the prevention program and to complete the assessments.
Study type	Randomized controlled trial
Date of first enrollment	June 2016
Target sample size	338
Recruitment status	Recruiting
Primary outcome(s)	Anxiety symptoms at T_2_, T_3_, T_4_; the Multidimensional Anxiety Scale for Children Depressive symptoms at T_2_, T_3_, T_4_; the Beck Youth Inventories™ -Second Edition for Children and Adolescents
Key secondary outcome(s)	Maladaptive cognitions at T_2_, T_3_, T_4_; the Children’s Automatic Thoughts Scale – Negative/Positive Comorbid problems at T_2_, T_3_, T_4_; the Strengths and Difficulties Questionnaire Prosocial behaviors Quality of life at T_2_, T_3_, T_4_; the Questionnaire for Measuring Health-Related Quality of Life in Children and Adolescents, The Revised Version – adolescent version Treatment expectancies at T_2_; the Credibility/ Expectancy Questionnaire Satisfaction with the intervention at T_2_; the Client Satisfaction Scale

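### The protocol says participants, researchers and assessors stay blinded, but participants and session leaders cannot be blind when attended class sessions are compared with an untreated waiting list, and both primary outcomes are self-reported

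*Protocol article*

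**What the plan says.** The section Randomization and blinding makes an unqualified claim: "Blinding of participants, researchers and assessors will be maintained". The same section places equal numbers of experimental and control groups within each school.

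The two conditions are described under Study conditions:

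- **Control:** "Participants in the waiting list will not receive an intervention". Access comes later, if at all: "They could receive the intervention after the experimental group has completed all the assessments".
- **Experimental:** "The program will consist of six 50 min sessions of video-based REBT", in a group format over three weeks, with homework between sessions. Of the first session the article says that "they will be informed about the program and about their involvement in this program".
- **Delivery:** "Research assistants (Masters students, psychologists trained in CBT) will present each session".

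Under Data collection, adolescents fill in paper questionnaires in their classrooms "in the presence of a research assistant, blind to group allocation", who helps if needed. Both primary outcomes (MASC for anxiety, the BYI-II depression subscale for depression) are completed this way. The limitations in the Discussion acknowledge reliance on self-report alone and the absence of a placebo condition.

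**The concern.** The blinding sentence credits the trial with a safeguard that its own description of the arms rules out. Blinding of participants matters most when participants produce the outcome data, and here they produce all of it. An adolescent who knows that he or she has taken part in a program, or is still waiting for one, may answer symptom questions differently for reasons of expectation or perceived demand. Such a difference would be part of the estimated group effect on both primary outcomes and could not be separated from it.

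What is at stake is how the result may be read. A difference described as coming from a trial with blinded participants supports a stronger conclusion than one from unblinded self-report against a waiting list.

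**Working it through.** No figure in the protocol rests on the blinding claim, so the check sets the statement against the rest of the article, one group at a time. The only calculation in the article, the sample size, does not depend on blinding and is unaffected by this point.

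**1. Participants.** The inputs are the two condition descriptions.
- One arm attends sessions, does homework and is told about the program in session 1. The other receives nothing until the experimental group has finished all assessments.
- There is no sham or attention control, and the Discussion concedes the lack of a placebo.
- Attendance itself therefore reveals the condition. With both arms in the same school, waiting-list classes are also near classes that receive the program.
- Result: the claim cannot hold.

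**2. Researchers.** The term is not defined.
- The people who present the sessions are called research assistants, and they know that the class in front of them is in the program.
- Result: the claim fails for session leaders. For other researchers, such as whoever analyses the data, the article neither shows that blinding fails nor says how it would be kept.

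**3. Assessors.** Data collection names one person, the research assistant present during completion, and says that this person is blind.
- Nothing in the article shows this to be unachievable.
- Result: the claim can stand for this person.

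**4. What the remaining blinding protects.** The assistant in the room does not score or rate symptoms. Adolescents answer the MASC and BYI-II items themselves, and the Discussion says that the trial relies on self-report only. The effective outcome assessor is thus the unblinded adolescent. Keeping the assistant blind limits differential help or prompting, but it does not protect the ratings from the adolescent's knowledge of the arm.

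**5. Whether the article corrects itself.** The limitations list self-report and the missing placebo. They neither withdraw the blinding sentence nor say that participants know their condition.

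**The case against.** The strongest defence is that this is one wrong sentence and not a flaw in the design. A waiting-list comparison could never have blinded participants, so no protection has been lost. The abstract names the control, so an alert reader can see that adolescents know their arm. The limitations already disclose self-report and the lack of a placebo, which are the two main ingredients of the expectancy problem. No arm, endpoint, sample size or analysis changes.

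Much of this stands. It makes the point a misstatement to correct and gives no reason to abandon the waiting list. It does not rescue the sentence, which asserts blinding without qualification and is not withdrawn anywhere.

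A reader might also infer several stronger things that the documents do not support:

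- **Session leaders also supervise the questionnaires.** The title research assistant is used for both roles, but no section says that the same people fill both. Five therapists and a separately described blind assessment role are compatible.
- **The satisfaction form unmasks the assessor.** Table 2 lists "Satisfaction with the intervention at T_2_; the Client Satisfaction Scale", but the article text does not say which classes complete it, in what order, or who hands it out. The overview figure of instruments is not available here.
- **The bias has a known size.** The documents give no value for a reporting shift, and any figure would be a guess.
- **Risk-of-bias assessors will be misled.** That is possible, but nothing in the documents establishes it.

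**Conclusion.** The blinding statement is wrong as written for participants and for session leaders. It is tenable for the assistant supervising the questionnaires, and undefined for other researchers. This conclusion rests on the article's own text and needs only one assumption: that adolescents know whether they have attended sessions.

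The consequence is qualitative. Both primary outcomes are unblinded self-report against an untreated control, so the trial can support a conclusion about the program versus waiting list on that kind of measure, without the protection that the sentence claims. No numerical size can be attached from the documents, and no planned figure needs recalculation. The point should be corrected because it bears on how the main result is interpreted.

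**What to change.** **Replace the blinding sentence.** State that participants and session leaders are not blinded. State that blinding applies to the research assistant who supervises the questionnaires and, where feasible, to the data analyst.

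**Add to the limitations.** Say that both primary outcomes are self-reported by adolescents who know their condition, so expectation and demand effects cannot be excluded.

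**Word the conclusion to match.** Describe the result as an effect versus waiting list on unblinded self-report.

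**Optional safeguard.** At T2, give the MASC and BYI-II before any satisfaction or expectancy form, in the same way in both arms. Recruitment was still open when the article was published, so this could be set for classes not yet assessed at T2.

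The cost is a change of wording, form order if the optional step is taken, and a less favourable risk-of-bias statement. Randomization, sample size and the analysis stay as they are.

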### Sample size calculation

A priori power analyses using G*Power version 3.1.5 [42] indicated that a total sample size of 260 would be sufficient to detect a small to medium effect size (*d =* .35) according to the results or previous research, for a two-tails between-group comparison at posttest, with an alpha of .05 and a power of 80%. As we expected to have a 30% dropout rate, we will recruit 169 participants in each group.

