**Methods:**

A two-arm parallel randomized controlled trial will be conducted, with two groups: a video-based transdiagnostic REBT universal prevention program and a wait list control. Power analysis indicated that the study will involve 338 participants. Adolescents with ages between 12 and 17 years old, from several middle schools and high schools, will be invited to participate. Assessments will be conducted at four time points: baseline (T_1_), post-intervention (T_2_), 3 months follow-up (T_3_) and 12 months follow-up (T_4_). Intent-to-treat analysis will be used in order to investigate significant differences between the two groups in both primary and secondary outcomes.

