### Design

A two-arm cluster randomized controlled trial (RCT) will be conducted. Participants’ school classes will be randomized by a computer software (www.randomizer.org) in one of the two treatment conditions: (1) video-based transdiagnostic REBT universal prevention program or (2) waitlist control. Assessments will be conducted at four time points: baseline (T_1_), post-intervention (T_2_), 3 months follow-up (T_3_) and 12 months follow-up (T_4_). Figure 1 illustrates the flowchart of the study.

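### The sample size of 260 is an individually randomised figure with no allowance for clustering, so the stated 80% power does not apply to this class-randomised trial

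*Protocol article*

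**What the plan says.** The title calls the trial cluster randomised. The Design section agrees: "A two-arm cluster randomized controlled trial (RCT) will be conducted", and "Participants’ school classes will be randomized by a computer software". The section on randomization and blinding is worded less clearly ("Randomization will be applied within classes, using a random numbers generator"), but the same sentence continues "with an equal number of experimental and control groups within one school", which describes allocation of whole groups. The intervention is also given to classes together, "delivered for three weeks (two times per week) in a group format".

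The Sample size calculation section uses G*Power for a two-sided between-group comparison at posttest, with d = .35, alpha .05 and power 80%. It concludes that "a total sample size of 260 would be sufficient to detect a small to medium effect size". It then allows for 30% dropout and arrives at 169 per group. The abstract repeats the result: "Power analysis indicated that the study will involve 338 participants". No ICC, class size, number of classes or design effect appears anywhere in the article.

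**The concern.** Adolescents in the same class share teachers, peers and, in the intervention arm, the same group sessions, so their outcomes tend to be correlated. When classes are the randomised units, this correlation inflates the variance of the treatment comparison, and the number of classes limits the degrees of freedom of the test. A calculation that treats adolescents as independent therefore overstates power.

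The section names its software, comparison, effect size, alpha, power and result. The matter is thus a stated figure that belongs to a different design, and not a detail left to a fuller document. It is also the only justification given for the trial's size. If the trial shows no difference, readers who accept 80% power at d = .35 will give that result more weight than the design supports.

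**Working it through.** **Inputs from the article.** d = 0.35; two-sided alpha 0.05; power 80%; 260 before dropout (130 per arm); 30% dropout; 338 recruited; classes randomised, with equal numbers of groups per arm within a school.

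**Inputs not in the article, hence assumed.** Class size m (15 to 30) and ICC (0.01 to 0.05).

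**Step 1: reproduce 260.** The noncentral-t solution for two independent groups is 129.1 per arm, rounded up to 130, so 260 in total. Power at 130 per arm is 80.3%. The normal approximation gives 129 per arm (258). A one-sided test would give 202, which does not match. So 260 is the independent-observations answer, with a design effect of exactly 1.

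**Step 2: add clustering.** The formulas are:

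- DE = 1 + (m − 1) × ICC
- effective N = N / DE
- noncentrality = 0.35 / √(4 × DE / N)
- degrees of freedom = N/m − 2

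Example for N = 260, m = 20, ICC 0.02: DE = 1 + 19 × 0.02 = 1.38; effective N = 260/1.38 = 188; noncentrality = 0.35/√(5.52/260) = 2.40; df = 13 − 2 = 11.

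The last column is the smallest d detectable with 80% power by normal approximation, 2.802 × √(4 × DE / N).

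| N analysed | m | ICC | DE | Effective N | Power, class-based t | Power, normal approx. | Detectable d |
|---|---|---|---|---|---|---|---|
| 260 | 20 | 0.01 | 1.19 | 218 | 65% | 74% | 0.38 |
| 260 | 20 | 0.02 | 1.38 | 188 | 59% | 67% | 0.41 |
| 260 | 20 | 0.05 | 1.95 | 133 | 45% | 52% | 0.49 |
| 338 | 25 | 0.02 | 1.48 | 228 | 68% | 75% | 0.37 |

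**Step 3: how small an ICC matters.** Using the more lenient normal approximation at 260, power falls below 78% at an ICC of about 0.005 (m = 15), 0.004 (m = 20), 0.003 (m = 25) and 0.0025 (m = 30).

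**Step 4: does 338 cover the gap?** 338 is 260 × 1.30. Allowing for 30% loss requires 260/(1 − 0.30) = 371.4, so 372. Conversely, 338 × 0.70 = 236.6. With about 237 analysed, power is about 76% to 77% with no clustering at all. At m = 20 and ICC 0.02 it is about 54% by class-based t (63% by normal approximation). If class size also shrinks by 30%, to 14, the normal approximation gives 67%.

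**Step 5: what baseline adjustment recovers.** Assume a T1–T2 correlation of 0.6 that acts only on the within-class variance. That part falls by 0.6² = 36%, and DE is replaced by 0.64 × (1 − ICC) + m × ICC. With 260 analysed in classes of 20, class-based power becomes about 80% (ICC 0.01), 72% (0.02) and 53% (0.05).

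**The case against.** Four arguments have some force.

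- **The trial recruits 338 and plans last observation carried forward, so all 338 enter the analysis.** With 338 fully observed, 80% can be reached at small ICCs: at m = 20 and ICC 0.01, power is 84% by normal approximation (79% by class-based t). It is therefore not true that every positive ICC takes the full recruited sample below 80%. This needs almost no dropout, however, while the plan expects 30%. Carrying a T1 value forward to T2 adds a record but no intervention effect.
- **The planned mixed models use repeated measures, and arms are balanced within school.** Both may help. Repeated measures can add precision, and balancing can remove between-school variance. Neither is part of the stated calculation, and correlation between classmates remains.
- **The size of the loss rests on an assumed ICC and class size, and 13 classes is an odd number although arms are to be balanced within schools.** This is correct. With 14 classes of 20 (280 analysed) and ICC 0.02, class-based power is 63%, so the conclusion does not turn on the layout. The direction of the error does not depend on these choices, but its size does.
- **The wording about randomising within classes could mean that individuals were allocated.** In that case the class-randomisation design effect would not apply. That reading conflicts with the title, the Design section and the reference to groups within a school. The wording should be reconciled, but it does not rescue the calculation.

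**Conclusion.** The concern holds. The stated 80% power at 260 is that of an individually randomised comparison, and this trial randomises classes. That 260 contains no clustering allowance is certain, because the figure reproduces exactly without one. That power at 260 in the stated posttest comparison is below the claim requires only an ICC that is not negligible (about 0.004 at m = 20 already takes it below 78%).

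The size of the loss is conditional. For 260 analysed in classes of 20 and ICC 0.01 to 0.05, power is about 65% down to 45% with class-based degrees of freedom, or 74% down to 52% by normal approximation. The recruitment target of 338 does not make this up under the plan's own dropout assumption.

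**What to change.** 1. Withdraw the 80% claim. State power, or the minimum detectable d, for the planned number of classes and class size over an explicit ICC range, for example 0.01 to 0.05. Use the number expected after dropout and degrees of freedom based on classes.
2. Describe 260 as the individually randomised figure.
3. Prespecify adjustment for the T1 score of each primary outcome. These scores are already collected, and adjustment recovers part of the loss.
4. Reword the randomization section so that the unit of allocation agrees with the Design section.

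The cost is a recalculation and some rewording, with no extra participants or assessments. The drawback is a less favourable stated power: at the higher end of the ICC range baseline adjustment does not restore 80%, and the text should say so.

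### The allowance for 30% dropout is too small: 338 recruits leave about 237 completers, not 260, so power for d = .35 is about 76% if that loss occurs by posttest

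*Protocol article*

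**What the plan says.** The Sample size calculation section of the protocol article reports a G*Power result: the analysis "indicated that a total sample size of 260 would be sufficient" for a standardized effect of d = .35, "for a two-tails between-group comparison at posttest", two-sided alpha .05 and 80% power. The next sentence makes the dropout allowance: "As we expected to have a 30% dropout rate, we will recruit 169 participants in each group". The inflation formula is not shown, and the section does not say at which assessment the 30% is expected.

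The total of 338 appears again in the Methods part of the abstract ("Power analysis indicated that the study will involve 338 participants") and as the target sample size in Table 2. Neither place gives a dropout rate or a power figure.

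The Statistical methods section plans an intent-to-treat analysis with the last observation carried forward, and mixed effects models.

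**The concern.** The section treats 260 as the number needed for the comparison and adds recruits because some will be lost. For that to work, the number recruited, less 30%, has to come back to 260. It does not: 30% of 338 is about 101, and about 237 remain.

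At stake is whether the stated 80% power is delivered under the plan's own dropout assumption. Bias and type I error are not affected. The consequence is a somewhat higher chance of missing an effect of the planned size, and a recruitment target that a reader would wrongly take to be protected against 30% loss.

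**Working it through.** **Inputs, all from the Sample size calculation section:** d = .35 (so SD = 1), two-sided alpha .05, power 80%, 260 in total (130 per arm), dropout 30%, 169 recruits per arm (1:1, 338 in total).

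**Step 1. Reproduce the 260.** Two-sample t-test with n per arm, 2n − 2 degrees of freedom and noncentrality d × √(n/2).
- The smallest n with power of at least 80% is 130 per arm, 260 in total. Noncentrality is .35 × √65 = 2.82 and power is 0.803.
- The normal approximation gives 129 per arm (258), which agrees closely. A one-sided test would give 204 in total and does not match.

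The 260 is therefore correct for individually randomized, independent observations.

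**Step 2. Reproduce the 338.**
- N × (1 + dropout): 260 × 1.30 = 338, or 130 × 1.30 = 169 per arm. This matches exactly.
- N / (1 − dropout): 260 / 0.70 = 371.4. Per arm, 130 / 0.70 = 185.7, so 186 per arm and 372 in total. Starting from 258, 258 / 0.70 = 368.6. Neither gives 338.

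**Step 3. What 338 leaves after 30% loss.**
- Completers: 338 × 0.70 = 236.6 (118.3 per arm).
- Shortfall against 260: 260 − 236.6 = 23.4 adolescents.
- Shortfall in recruits: 372 − 338 = 34.
- Check of the divided form: 186 × 0.70 = 130.2 per arm, which restores the 130.

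**Step 4. Power among completers at d = .35.**

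| Completers per arm | Dropout from 169 | Power (noncentral t) |
|---|---|---|
| 130 (the requirement) | 23.1% | 0.803 |
| 126.75 | 25% | 0.793 |
| 118.3 | 30% | 0.764 |

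Rounding to 118 or 119 per arm gives 0.763 to 0.767. The normal approximation at 118.3 gives 0.768. The effect detectable with 80% power rises from d = .349 at 130 per arm to d = .366 at 118 per arm.

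**Step 5. Dropout that 338 does cover.** 1 − 260/338 = 0.231. Up to about 23% loss, 260 completers remain.

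**The case against.** **Timing of the dropout.** The power statement is for posttest, which follows a three-week programme. The section does not say when the 30% is expected, and the only discussion of when dropout may occur, under Discussion, concerns the 12-month assessment. If 30% is cumulative to 12 months and posttest loss is smaller, the posttest claim survives. At assumed posttest losses of 10%, 15% and 20%, power with 169 recruited per arm is 86%, 84% and 82%. This objection stands. A reader might infer that the 80% is missed outright, but the document does not establish that; the shortfall applies where loss is 30%. Still, the single 30% rate sits in the paragraph that powers posttest, so the natural reading applies it there. Table 2 also lists the 12-month assessment as a primary time point.

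**Last observation carried forward.** Dropouts stay in the planned analysis, so a reader might infer either that only 237 will be analysed or, conversely, that all 338 give full protection. Neither follows. The 237 are completers, and 76% is the power of a completer t-test, not of the planned analysis. With all 338 and an undiluted effect, power would be 0.894, but carried-forward baseline values carry no treatment effect. As an illustration, assume every dropout carries a baseline value, shows no group difference, and the SD is unchanged. Then d falls to .35 × 0.70 = .245 and power with 169 per arm is about 0.61. Carrying values forward therefore does not rescue the 80%.

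**Clustering matters more.** The Design section randomizes school classes, while 260 comes from an individual-level calculation. With assumed classes of 20 to 25 and an assumed intraclass correlation of .01 to .05 (neither is in the article), power at the full 130 per arm would be about 73% to 47%. This is fair: the dropout step is the smaller part of the sample-size problem. It is nevertheless a separate error and does not depend on any clustering assumption.

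**Conclusion.** The point holds as a modest correction of a stated figure. The dropout step appears to multiply by 1.30 where division by 0.70 is needed. The formula is inferred, but the match is exact and the divided form does not give 338. If 30% are lost by posttest, 338 recruits leave about 237 completers and about 76% power for d = .35, roughly 4 points below the stated level, before any design effect. If posttest loss is about 23% or less, at least 260 remain and the stated power stands on its own individual-level terms.

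A reader might also infer that the abstract and Table 2 are wrong. They are not, as long as the target stays at 338: both give only the total, with no dropout or power figure to correct.

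**What to change.** Restate the Sample size calculation section along these lines: 338 recruits with 30% dropout leave about 237 completing at posttest and about 76% power for d = .35, before any design effect; 80% power holds only if dropout is at most about 23%. Say completing, not analysed, because dropouts remain in the intent-to-treat analysis. Also state the assessment to which the 30% applies. The expected dropout should not simply be relabelled as 23% to fit 338, since the article gives no basis for that rate.

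The cost is about one sentence and a slightly less favourable power statement, with no added enrolment and no change to design or analysis.

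If the sponsor prefers to keep both 80% power and the 30% allowance, the target becomes 372 (186 per arm), 34 more recruits. The Trial status section says recruitment is still ongoing, so this was open when the article was written. Only in that case would the abstract and Table 2 need to change. Either correction leaves the effect of class randomization still to be dealt with.
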